#### Patient study arm- qualitative

For an in-depth exploration of individual perceptions of problems and solutions, semi-structured interviews will be carried out and this process will help define the beliefs, behaviours, attitudes and sensitivities of patients in the different study cohorts. For the qualitative strand, a purposive sampling technique will be employed. The strategy best used in our study is one of maximal variation sampling, such that diverse individuals are chosen who are expected to hold diverse perspectives on the central theme, and their views will reflect a rich and complex picture of the reality. The qualitative idea is not to generalize from the sample but to obtain an in depth understanding of the issues in a few people who have been sampled, unlike the quantitative study arm.

The study sample will comprise pre-dialysis patients (Cohorts A + D), home haemodialysis patients (Cohort C) and hospital haemodialysis patients (cohort B). All adult patients aged 18 and over, with end stage renal diseases, who meet the inclusion criteria and no exclusion criteria, will be considered eligible for the study. The aim is to conduct about 20 interviews in each cohort or until thematic saturation is attained.

A recruitment grid is designed taking into consideration three factors- age, gender and ethnicity. Although it is not a requirement for recruitment, every effort will be taken to include patients with varying comorbidity profile. English, Hindi and Urdu speaking patients would be considered, representing the local population demographics.

Participants will be approached at their regular clinic consults by researchers with the study information leaflet and consent form. Where the patient expresses a willingness to consider participation, telephone contact will be made after a minimum of 24 hours of providing information. At this time, any questions will be answered and if the participant remained willing, an appointment for the interview will be scheduled. In a majority of instances this would be in the patient’s own home or at the patient’s request, the venue would include the hospital. Suitably qualified individuals will carry out the interviews. All interviews will be one-to-one. They will be audio-taped and then transcribed verbatim.

For purposes of the study, an interview schedule or topic guide has been developed with a view to cover the following areas-

a. Barriers and enablers of home haemodialysis as patients perceive them

b. The potential solutions as seen by patients

c. Impact of self-cannulation on decision-making

d. Views on assisted home haemodialysis

### Carer study – qualitative

#### Participant eligibility (carers)

All adult carers (aged 18 and over) of patients undertaking home haemodialysis or carers of patients who are in the decision-making process, who meet the inclusion criteria and none of the exclusion criteria will be considered eligible for this study.

#### Carer Inclusion criteria

Participants are eligible for INCLUSION in the study if the following criteria are met-

–The patient needs to consider the individual to be their carer.

–The individual self-defines themselves as the patient’s carer.

For the purposes of this research, a broad definition of the carer’s role is employed. A carer in the context of home haemodialysis is understood to range from providing emotional support to the patient, to taking a degree of responsibility for the patient’s dialysis procedure (Blogg and Hyde, [1]).

#### Carer exclusion criteria

Participants will be EXCLUDED from the study if, in the opinion or knowledge of the interviewer, either of these criteria is present:

–An established primary care diagnosis of psychiatric illness

–A life-threatening physical illness

The participant information sheet will be provided to the participant, to make an informed decision concerning in the study. A copy of the signed informed consent and information sheet will be given to the carer. Carers will undertake semi-structured interviews, at a place of their choosing- their homes or at the hospital. About 20 carers will be interviewed or until thematic saturation is attained. All interviews will be audio-taped and transcribed verbatim. Adequate steps will be undertaken to ensure that distress, if any, caused to them when they verbalize their fears will be dealt with appropriately and professionally.

### Provider study arm – qualitative

Alongside patient assessments, investigators will obtain information pertaining to the centres offering home haemodialysis. More specifically, this study seeks to help policymakers and renal care providers to understand and overcome barriers to delivering complex, patient-led medical procedures in the home by addressing the organizational, financial and policy influences on the uptake of HHD. This research project investigates how regulation, reimbursement rules and health policy impacts the provision of care for patients with chronic kidney disease.

Specific questions which will be posed include-

1. What factors impact on the adoption of technological innovations in renal care, especially home haemodialysis?

2. How do factors such as cost and financial arrangements (e.g. payment, incentives or penalties), implementation (e.g. training), intra-organisational issues (e.g. clinical leadership, resistance of incumbents to innovation), or environmental context (e.g. space at home, distance between home and clinic) limit the use of home haemodialysis to a level far below of what is generally considered desirable?

3. What impact do financial regulatory changes (e.g. PbR and the ‘best tariff practice’ in the UK, bundling of services and changes to reimbursement rules for home haemodialysis in the US) have on the behaviour of healthcare professionals and on care provision?

4. What impact will different policy choices and payment regulations likely have on the use of different dialysis modalities in the future?

#### Research approach

This study will combine qualitative research through interviews with modeling. The interviews will address research questions 1, 2 and 3 and modeling will address question 4.

#### Design

This is a comparative multi-centre study. It will employ qualitative methodology in the form of 45 to 60 minutes in-depth semi-structured interviews. Data from the qualitative case studies and background interviews will be used to inform simulation modeling exercises to investigate the implications of implementing HHD under differing policy and financing options, and with differing care provision models.

#### Respondents

The background interviews will involve selected participants from leading (i) dialysis service organizations, (ii) dialysis machine design and manufacturing firms, (iii) national renal policy-making bodies.

The case studies interviews will involve (i) healthcare professionals, (ii) managers of selected renal care centers. The aim is to interview all personnel involved in the modality decision making process as well as the care of renal patients in each centre. These include:

•Physicians

•Nurses

•Medical/Clinical directors

•Commissioners

## Economic evaluation

Although the study is not powered to evaluate a definitive economic benefit of HHD, we will estimate costs related to hospitalizations, medications and cost-utility from the provider’s perspective based on data from at least 2 case-study sites. The study will analyse the incremental costs of providing HHD, including direct costs (disposables, equipment, personnel, training, monitoring and technical services) and in-centre costs (HD unit overhead). We will also explore the potential impact of policy choices and financial conditions on HHD implementation under a variety of scenarios. We will use simulation modeling to analyse such impacts on patient flows through the system, the choice of dialysis modality and costs.

### Provider study arm-quantitative

From the different centres participating in the study, centre specific information will be obtained. The broad areas where detailed information will be sought include-

a. Infrastructure

b. Predialysis education and preparation

c. Training for HHD

d. Post-Discharge support structure

#### Dialysis unit staff-attitudes and practices (Organizational Culture Inventory®)

Understanding the collective thought processes informing a certain type of practice or behaviour is fundamental to effecting the desired change. The use of a quantitative instrument together with ethnographic approach followed by triangulation of results is likely to give a more complete picture of the practice in a unit. Such an approach in an area like dialysis methods has not been undertaken before and would add value to the information available. ‘The main appeal of such a method, lies in seeking to engage organizations and their problems on the level of meaning’ [41]. One may not assume that everyone has a similar understanding of the issues and may have opinions and judgments that vary from the perceived norm.

This Inventory by Cooke and Lafferty, is a quantitative measure of the culture in the unit/organization [42]. It evaluates the shared norms and expectations that guide thinking and behaviour of group members. It has previously been employed in the healthcare sector. It has 120 pre-defined questions and will have 20 additional questions introduced specific to the study context. The responses are made in a 5 point Likert scale. It is likely to take up to 20–25 minutes for completion. The tool has good face validity, and strong psychometric underpinning. Results can be graphically illustrated. The problems may be encountered with the length of the tool, but sufficient time will be given to staff to engage with this tool, as we investigate its application in a novel context.

### Data protection

Each patient enrolled into the study, is assigned a unique identification number. All personal identification data are stored in hospital computers only and separated from medical and research data. Biological samples are identifiable only with their unique sample identifier and no patient identifiers are available within the Biobank. All information pertaining to OCI® from specific centres are only known to the lead researcher and not available to the organisation that holds the license to conduct the survey.

### Quality assurance

In order to ensure consistent performance across all centres, single researcher (AJ) has conducted induction days across all centres. The database will be continually cleaned and examined to ensure data entry is accurate and missing data is minimised. The database is backed up regularly to ensure no loss of data. Biological samples obtained are collected, processed and stored in appropriate conditions and by certified personnel. All qualitative aspects of the study will be reviewed by at least two qualified researchers. All costs related information will be procured after checking relevant documents from appropriate authorities.

### Enrolment to-date

Enrolment as of the end of April 2013 comprises a total number of 350 patients across five centres. It is anticipated that the recruitment period will end in late 2013. Recruitment for the qualitative aspects of the study is about 75% complete.

### Data analyses and statistical considerations

#### Quantitative data analysis

The sample size of the BASIC-HHD study of 500 patients was chosen as a realistically attainable cohort size based on feasibility considerations. This sample size ensures adequate statistical power to differentiate cohorts showing different behaviours with respect to the primary and secondary objectives. The power analysis is also based on the effects expected in the clinical measures.

Demographic data will be reported using means and standard deviations (for normally distributed data) or median and interquartile/full ranges (for skewed data) where appropriate. Simple comparisons between baseline data from the three study cohorts will be made using two-sided tests; analyses of variance for normally distributed data, Kruskal-Wallis for non-normal continuous data and ordinal data, and chi-square tests for categorical data, with the conventional 5% significance level. Individual cognitive test scores will be reported as mean and standard deviations. Scores will be reported both as normalized scores. In normalized scores, data are fit to a normalized scale allowing direct comparisons across scores. Factors which influence uptake and maintenance will be identified using multiple logistic regression analysis of the pre-dialysis cohort. Comparisons between the HHD (C) and Hospital HD (B) cohorts will use t-tests, Mann–Whitney U-tests and chi-square tests as appropriate, followed by multiple logistic regression analysis to identify significant independent discriminatory factors. The study will have 80% power to detect differences in the percentage of patients having particular factor attributes of 19% or more between the age-sex matched cohorts of 100 patients (i.e. 20% vs. 39%, equivalent to an odds ratio of approximately 2.5). For the pre-dialysis patients, of whom 10% are estimated to take up home haemodialysis, the study will have 80% power to detect prognostic factors with an odds ratio of 4 or more for the whole cohort of 200 patients.

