### Study objectives

The primary objective of the BASIC-HHD study is to conduct a comprehensive and systematic study of the barriers to and enablers of successful uptake and maintenance of HHD across multiple centres with low, medium and high prevalence rates of home HD. Care pathways of predialysis, incident and prevalent dialysis patients will also be investigated under clinical, psychosocial and organisational domains.

Additionally, the secondary objectives are, to

a) Investigate biomarkers and their links to cognitive attributes utilised in decision making in ESRD.

b) Analyse scenarios of the uptake of different dialysis modalities over time and assess the impact on service design (based on system dynamics modeling)

c) Assess impact of centre infrastructure, policy and regulations on implementation dynamics of HHD

d) Conduct an economic evaluation to examine efficiency savings and value

e) Evaluate carer perspectives and burden in the treatment journey of the patient

We believe that such study of HHD uptake, examining barriers and drivers at various levels, using a multi-layered approach that examines patient and organisational factors in parallel using mixed methods (parallel and convergent design) is an ideal methodology to address the research question. A comprehensive study, would aid development of a model of adoption of HHD, which would incorporate variables from both qualitative and quantitative studies. This is the overall aim of the proposed BASIC-HHD study.

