#### Collection of biological samples

Samples will be sent to the Renal Research Labs for processing and storage. DNA, plasma, cells and a clinical/demographic data set will be held in the laboratories for research, with patient consent. The samples will be obtained from patients at the host centre and frozen in the biobank storage at −80°C, within two hours of collection. This is with a view to study uraemic ‘neuro’toxin assays in these patient cohorts. This remains the subject of a further study relating neurochemistry and behavioural biology. Many of the biochemical parameters being evaluated would be obtained routinely during the course of their medical management and would help in quantifying treatment and disease burden and illness related complications. These samples will be analysed at the South Manchester University Hospital laboratory (Figure 3).

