#### Study outcomes

The quantitative and qualitative studies which are being undertaken to understand patient clinical and psychosocial parameters, in the context of healthcare infrastructure and provider views from geographically distinct sites, will give the breadth and depth of problem perception and solutions. We seek to identify systemic issues that may deter the uptake of HHD and understand factors which may define the atlas of variation, to develop a tool to implement a practice changing model of care. Additionally, the study will highlight the beliefs and concerns of the major stakeholders- patients, care givers and healthcare providers on HHD. We will be able to ascertain the range of interventions and assistance that may be necessary for successful adoption. The association (if any) between patient-psychosocial factors and biochemical parameters, including specific toxin assays in the context of ESRD will also be analysed. The study findings will be disseminated to clinicians, organisations and health care strategists as guidance to inform future policy. Lessons from the implementation of the study design would also pave way for more holistic research of chronic diseases in health care systems using this methodology.

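### The power claim covers the secondary objectives without exception, yet the protocol says its economic evaluation, a secondary objective, is not powered for a definitive benefit

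*Protocol article*

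**What the plan says.** All references are to the protocol article.

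- **Quantitative data analysis.** The total of 500 "was chosen as a realistically attainable cohort size based on feasibility considerations". The next sentence turns that into a statement about power: "This sample size ensures adequate statistical power to differentiate cohorts showing different behaviours with respect to the primary and secondary objectives". Two figures follow later in the same section. One is 80% power for a difference of 19 percentage points (20% versus 39%, odds ratio about 2.5) between age-sex matched cohorts of 100. The other is 80% power for an odds ratio of 4 or more in the 200 pre-dialysis patients, of whom 10% are expected to take up home haemodialysis.
- **Study objectives.** Secondary objective (d) reads "Conduct an economic evaluation to examine efficiency savings and value". The other secondary objectives are (a) biomarkers and cognition, (b) scenario modelling of modality uptake, (c) the effect of centre infrastructure and policy, and (e) carers' perspectives and burden.
- **Economic evaluation.** "Although the study is not powered to evaluate a definitive economic benefit of HHD", costs and cost-utility will be estimated from two or more sites.
- **Collection of biological samples.** For the stored material, "The samples will be obtained from patients at the host centre". The section leaves the neurotoxin assays to a separate, later study.
- **Study outcomes.** The association between psychosocial factors and biochemical parameters, "including specific toxin assays in the context of ESRD will also be analysed".

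**The concern.** A power statement is a claimed property of the design, and readers use it when they interpret a null result. Here the claim reaches every secondary objective, while another section withdraws it for one of them. Someone who reads only the statistical section could take an inconclusive cost comparison as evidence of no difference from an adequately powered study. This matters somewhat more because the findings are meant to inform policy.

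The move from feasibility to assurance adds to the difficulty. The number was chosen as what could be recruited, and such a number can still be adequate for particular comparisons. That has to be shown comparison by comparison, and the article shows it for two.

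**Working it through.** **1. First power figure.** Inputs from Quantitative data analysis: p1 = 0.20, p2 = 0.39, 100 per group, 80% power. The two-sided 5% level is stated for the baseline comparisons ("with the conventional 5% significance level") and is assumed here for the power figures too.

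Mean proportion = (0.20 + 0.39)/2 = 0.295; difference d = 0.19.

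n = [1.96 × √(2 × 0.295 × 0.705) + 0.8416 × √(0.20 × 0.80 + 0.39 × 0.61)]² / 0.19² = (1.264 + 0.531)² / 0.0361 = 89.3, so 90 per group.

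With continuity correction: (89.25/4) × [1 + √(1 + 4/(89.25 × 0.19))]² = 99.5, so 100 per group.

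Power at 100 per group is 84.3% without the correction. With it, z = (0.19 − 0.01 − 0.1264)/0.0631 = 0.85, which gives 80.2%. The odds ratio is (0.39/0.61)/(0.20/0.80) = 2.56. The article's figure reproduces.

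**2. Second power figure.** Inputs from the same section: N = 200, overall uptake 10%, odds ratio 4. The prevalence of the factor is not given, so it is an assumption and is varied. For each prevalence f, the uptake rates p0 (factor absent) and p1 (factor present) solve (1 − f)p0 + f·p1 = 0.10 with an odds ratio of 4. The power is that of the two-proportion test without continuity correction.

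| Factor prevalence (assumed) | p0 | p1 | Power |
|---|---|---|---|
| 10% | 0.082 | 0.263 | 66% |
| 20% | 0.068 | 0.227 | 79% |
| 30% | 0.058 | 0.198 | 81% |
| 40% | 0.050 | 0.175 | 80% |
| 50% | 0.044 | 0.156 | 75% |
| 60% | 0.039 | 0.140 | 67% |

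The stated 80% is reached, or nearly so, between about 20% and 40% prevalence.

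**3. Scope.** The remaining step is a comparison of passages.

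- The power sentence covers the primary and the secondary objectives and makes no exception.
- Study objectives places the economic evaluation among the secondary objectives, as (d).
- The Economic evaluation section says that the study lacks power for a definitive economic benefit.
- The two figures checked above concern patient factors. Neither is stated for costs or cost-utility.

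The first and third statements cannot both hold for objective (d). No power can be computed for that objective, because the article gives no cost difference or variance.

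**The case against.** The strongest reply is that the sentence speaks of differentiating cohorts, stands under the quantitative analysis of 500 patients, and is followed by two figures on patient comparisons. On that reading it was never meant to reach costs, modelling or carer interviews. Moreover, the economic limitation is stated openly where the economic work is described, so a reader of that section is not misled. Both points have weight and are why this is minor. They do not remove the conflict, because the sentence itself names the secondary objectives and one of those is the economic evaluation.

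Three stronger readings are tempting, and the article does not support them.

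- **A reader might infer that one-centre toxin sampling makes the power sentence false.** It does not. Collection of biological samples assigns the neurotoxin assays to a later study, and the Discussion lists them among planned studies. Objective (a) speaks of biomarkers in general, and many of the biochemical parameters come from routine care. No power is claimed for toxins. The number of host-centre patients is not given, so any detectable effect for that subset would rest on a guess.
- **A reader might infer that five centres are too few for objective (c).** That would matter for a test across centres. The article plans none: it describes interviews, case studies, centre information, a staff culture inventory and simulation.
- **A reader might object that no expected effect on a clinical measure is given,** although the power analysis is said to draw on such effects. A condensed article may leave that detail to the full protocol.

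**Conclusion.** The concern holds as an overstatement of scope. The power sentence claims more than the article supports, and the Economic evaluation section contradicts it for secondary objective (d). This conclusion needs no outside figure or assumption.

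The two power figures are not in dispute. The first is confirmed at 80.2% with continuity correction, given a two-sided 5% level. The second is attainable if the factor's prevalence is roughly 20% to 40%. Nothing here shows the power claim to be wrong for those two patient-factor analyses.

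A separate and smaller inconsistency concerns the toxin assays, which are left to a later study in one section and listed under Study outcomes in another. It has no bearing on the power sentence.

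Severity: minor.

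**What to change.** 1. In Quantitative data analysis, remove the secondary objectives from the power sentence and tie the claim to the two analyses with figures: the matched-cohort comparison (100 per group, 20% versus 39%) and the predictors of uptake in the 200 pre-dialysis patients (odds ratio of 4 or more).
2. Add a sentence saying that the economic evaluation and the other secondary objectives are estimated or descriptive and not powered, with a pointer to the Economic evaluation section.
3. Reconcile Collection of biological samples with Study outcomes: say whether the toxin assays are an outcome of this study or belong to the later one. If they are an outcome here, say that the stored samples come from the host centre.

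The cost is a few words and a less favourable claim about power. Sample size, data collection and analyses do not change, so the correction can be made although 350 patients were already enrolled by the end of April 2013.

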The Illness Perception Questionnaire-revised (IPQ-R) assesses the following illness perceptions- identity, chronic timeline, cyclical timeline, treatment control, personal control, coherence, causes and emotion reaction. Across several illnesses, the reliability and validity of the IPQ-R has been demonstrated [34]. There is now evidence towards the validity and reliability of the IPQ-R as suitable measure of illness perceptions in the context of ESRD [35,36]. Illness perceptions drive coping and self-management behaviours and hence are an important measure in this study. Home modalities of renal replacement therapy, are very demanding of memory. Beliefs about one’s potential to use memory efficiently will influence self-selection of such therapy [37,38]. Also, individual differences in self-rated memory do not correlate well with objective memory tests- this may imply that people’s beliefs about their memory are inaccurate [39]. This is at least true of the general population. The metacognition questionnaire has two components - the meta-memory and meta-concentration. Additionally, this questionnaire has items worded that are consistently ‘positive’ and avoid a deficit connotation [40]. This has been used in elderly patients, but the questions have no specific age-focus and are applicable to the ESRD population, for the purpose of this study.

To allow for a comprehensive understanding of cognitive function, multiple measures must be included in the neuropsychological test battery. The tests would consider different domains of brain function- psychomotor efficiency and processing speed, learning efficiency and attention. Greater understanding of patient’s cognitive state can be attained through combining subjective cognitive function, for self-reported everyday functioning, in addition to the cognitive psychometric tests. The neuropsychometric tools to be employed are: 3MS/Trail making tests and Digit span test. All neuropsychometric tests and the meta-cognition questionnaire will be conducted in the mid-week, pre-dialysis phase for dialysis patients. This helps standardise the data collection across all centres. All sighted and literate patients will be invited to participate in these tests.

In addition to the outcomes of questionnaire based psychosocial outcomes, any potential association with readily measurable biomarkers could inform day to day clinical management of patients presenting in advanced CKD clinics.

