The BASIC HHD is a pragmatic study, suitably equipped with requisite expertise to carry out the work. We have invested the effort and time to form a team of researchers who are keen to study several facets of the research question in parallel, from across UK. Prospective recruitment of the pre-dialysis cohort will help understand the patient journey better and we anticipate recruiting patients from across the spectrum of illness severity. This will improve the generalizability of our findings. Bias and random error in handling data will be minimised by validation checks by the researcher on data entry by research nurses. Periodic visits to the participating units will ensure uninterrupted and uniform data gathering, and an opportunity to troubleshoot problems as they arise. Conceptually, the BASIC-HHD study is intended to be both confirmatory and exploratory in design and provide a scaffold for ancillary studies addressing specific psychosocial characteristics and biomarkers in the different study cohorts. Planned studies include an in-depth characterization of uraemic ‘neuro’toxins, namely the guanidino compounds and their impact on cognitive outcomes and decision making processes in ESRD. Exploratory work in search of a candidate biomarker in biological samples (Blood spots and saliva) for cognitive dysfunction in the context of ESRD is underway. It is also likely that progression of the ‘uraemic state’ impacts on physical factors such as, global DNA methylation, gene expression and metabolic pathways, which may influence mental health and quality of life. Its associations with psychological outcomes can now be combined to generate valuable information, for patient care.

In conclusion, the BASIC-HHD is a unique study in dialysis medicine, which will assemble pivotal information on dialysis modality choice and uptake, investigating users, caregivers and care delivery processes and study their variation in a multi-layered analytical approach within a single health care system. The study results would define modality specific service and patient pathway redesign with the potential of a paradigm shift in practice and providing future directions in dialysis care.

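### The home haemodialysis uptake regression expects about 20 events against about 27 candidate scores, and its stated power covers one factor only

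*Protocol article*

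**What the plan says.** All analysis statements are in the Quantitative data analysis section of the protocol article, which describes three steps.

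- **Three-cohort baseline comparisons.** These "will be made using two-sided tests", "with the conventional 5% significance level".
- **Uptake and maintenance.** Influencing factors are to be found by multiple logistic regression in the pre-dialysis cohort. Of these patients, 10% are expected to take up HHD. The power given is 80% for an odds ratio of 4 or more in the whole cohort of 200.
- **HHD (cohort C) versus hospital haemodialysis (cohort B).** Two-group tests come first, "followed by multiple logistic regression analysis to identify significant independent discriminatory factors". The power statement reads: "The study will have 80% power to detect differences in the percentage of patients having particular factor attributes of 19% or more". It applies to two groups matched on age and sex, each of 100, and the example behind it is 20% against 39%, an odds ratio of about 2.5.

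The Instruments section lists the questionnaires and cognitive tests. The illness perception questionnaire alone "assesses the following illness perceptions- identity, chronic timeline, cyclical timeline, treatment control, personal control, coherence, causes and emotion reaction". Under Patient participants, about 100 HHD patients are expected, and about a third of the pre-dialysis cohort is expected to start dialysis within 12 months. The Discussion says that "the BASIC-HHD study is intended to be both confirmatory and exploratory in design".

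**The concern.** Both regressions are meant to identify factors, and for C versus B the criterion is explicitly significance. The uptake model has few events for the number of scores collected. Ordinary maximum-likelihood logistic regression with many predictors and few events pushes odds ratios away from 1. Picking factors by significance from a long list also produces false ones.

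The power statement can hide this. An odds ratio of 4 at 80% power reads as a property of the uptake analysis, but it describes one factor tested alone. The Study objectives section sets the overall aim as a model of HHD adoption that takes in variables from the quantitative arm, so spurious or overstated factors could be carried into it.

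**Working it through.** **1. The plan's own power figures.**

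- *C versus B.* For 20% vs 39%, two-sided 5% and 80% power, the normal-approximation sample size is 90 per group without and 100 with continuity correction. The odds ratio is (0.39/0.61)/(0.20/0.80) = 2.56. The stated figure reproduces.
- *Uptake.* Solve two risks that give an odds ratio of 4 and 10% uptake overall. If 30% of patients have the factor, the risks are 5.8% and 19.8% (0.7 × 5.8% + 0.3 × 19.8% = 10%), and power at N = 200 is 81.3%. At factor prevalences of 20%, 40% and 50% it is 78.5%, 80.0% and 75.4%. The stated figure reproduces for prevalences of about 20 to 40%, for one factor at 5%.

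**2. Candidate scores (Instruments section).**

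| Instrument | Scores |
|---|---|
| SF-36 | 8 |
| Illness perceptions | 8 |
| Depression | 1 |
| Anxiety (state, trait) | 2 |
| Metacognition | 2 |
| Attachment style | 1 |
| Autonomy preference | 1 |
| 3MS | 1 |
| Trail making | 2 |
| Digit span | 1 |
| **Total** | **27** |

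The total is 26 if trail making is one score and 28 if autonomy preference is two. Clinical, demographic and laboratory variables come on top.

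**3. Events per candidate.**

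- Uptake: 0.10 × 200 = 20 events, and 20/27 = 0.74.
- Uptake, if the 10% applied only to the third who start dialysis: 200/3 ≈ 67 patients, 0.10 × 67 ≈ 7 events, and 6.7/27 = 0.25.
- C versus B: 100/27 = 3.7.

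**4. Chance findings, one test per score, no true effects.** With independent scores, 27 × 0.05 = 1.35 false positives are expected and the chance of at least one is 1 − 0.95^27 = 75%. With a common correlation of 0.3 it is 63%, and with 0.5 it is 48%.

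**5. Simulated regressions, all 27 scores entered, correlation 0.3, one true odds ratio of 2 per SD.**

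| Model | Median estimated OR | Fits with a false factor |
|---|---|---|
| Uptake, 20 events in 200 | 2.7 to 2.9 (3.2 when significant) | 81 to 82% |
| Uptake, about 7 events in 67 | 99% of fits separate or fail | – |
| C versus B, 100 vs 100 or 100 vs 200 | 2.2 | 76 to 79% |

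The range in the first row spans two separate simulations. At 20 events, 10 predictors or fewer give a median of about 2.1. Firth regression gives about 2.0. A model with two pre-named factors shows a false factor in 6% of fits.

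**6. Simulated univariate screening at p < 0.05, then regression (entry rule assumed).** With no true effects, a false independent factor appears in 73% (20 events) and 74 to 77% (C versus B) of runs if scores are independent, and in 41 to 43% at correlation 0.3. Screening nearly removes the inflation: the median significant odds ratio at 20 events is 2.1 to 2.2.

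**The case against.** The strongest objection is that the article never says all 27 scores enter one model. For C versus B it puts two-group tests first, and for uptake it gives no candidate list. Candidate lists, selection rules and multiplicity control are commonly left to a full protocol or analysis plan, which is not shown. This stands: their absence is not the finding, and the inflation to 2.7 to 2.9 is conditional on entering everything. What remains is what the article does fix: the method, the expected event count, significance as the C versus B criterion, and a one-factor power figure. The false-factor risk does not need forced entry, as step 6 shows. It is not constant either: with one true factor and correlation 0.3, screening leaves a false factor in only 10 to 21% of runs.

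A reader might also infer more than the text supports:

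- **That the significance-based search rests on 20 events or fewer.** That sentence belongs to C versus B, with about 100 HHD patients. The low count applies only to the pre-dialysis model.
- **That chance findings are nearly certain.** Steps 4 to 6 do not reach that, and the quality-of-life, depression and anxiety scales would be expected to correlate.
- **That 5% is the entry rule for the regressions.** It is stated for the three-cohort baseline comparisons.
- **That the study calls these analyses confirmatory.** It calls itself both confirmatory and exploratory and does not say which analyses are which.
- **That only 7 events are planned.** The article applies 10% to the pre-dialysis patients, which gives 20.

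Finally, the adoption model also draws on qualitative work, and the simulation modelling uses registry, interview and literature sources. These odds ratios are not its only input.

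**Conclusion.** The point holds in a limited form. About 20 expected HHD events can support only a few factors in the uptake regression, and the stated 80% power for an odds ratio of 4 applies to one factor tested at 5%. If only the roughly 67 patients who start dialysis were informative, that power would be about 33 to 43%.

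How much harm follows depends on how many scores enter. Bias is substantial with all 27 and small with 10 or fewer. A false independent factor appears in about 80% of fits with all 27, and in about 40 to 75% under screening when no score has a true effect. The C versus B model shares the false-factor risk but not the serious inflation. These figures rest on normally distributed scores, a common correlation of 0 or 0.3 and, where one is included, a true odds ratio of 2 per SD. This is a worthwhile, inexpensive improvement and not a flaw that invalidates the study.

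**What to change.** 1. **Uptake model.** Pre-name about two to four factors (20/2 = 10 to 20/4 = 5 events per factor) and fit them by Firth penalised logistic regression. Both parts are needed: Firth removes most of the bias in the odds ratios, and the short list controls false factors.
2. **Power statement.** Say that 80% power for an odds ratio of 4 refers to one pre-named factor at 5%.
3. **Everything else.** Label the other score-by-score comparisons and the C versus B factor search as exploratory, and report how many scores were tested. False-discovery-adjusted p-values can be shown alongside if wished.

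A strict family-wise correction is not proposed. Bonferroni over 27 scores (0.05/27 = 0.00185) would cut power for 20% vs 39% with 100 per group to 43%. One summary score per construct, or lasso for C versus B, is a matter of choice and can be left to the analysis plan.

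The cost is a change of wording and a little programming, with no extra patients or data. The downside is that fewer factors can be claimed as independent predictors of uptake.
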